### Group allocation and blinding

Participants will be assigned using blocked stratified randomization with allocation concealment to one of two training groups: 1) perturbation training, or 2) ‘traditional’ balance training (control). To maintain allocation concealment, a variable block size ranging from 4–8 will be used. There will be four strata based on two stratification factors: site (two levels), and frequency of ‘failures’ during baseline reactive balance control assessment (two levels). Stratification by site will ensure that the treatment groups are balanced within each institution accounting for potential differences in intervention administration between sites. Balance recovery ‘failures’ are defined as use of the overhead support harness and/or research assistant to prevent a fall to the floor, or stepping with the blocked limb during the encouraged-use condition; high frequency of failure predicts falls in the community [27]. Frequency of failures will be classified as either ‘high’ (≥10 % of trials) or ‘low’ (<10 % of trials). This approach will help to ensure that the groups do not differ significantly on this prognostic factor [38, 39], particularly within each site, and that there will be approximately equal numbers of participants assigned to each group. Group allocation will be performed centrally by the principal investigator, who will not be involved in recruiting, assessments, or administering the interventions. The random allocation sequence will be computer generated and maintained in an electronic file by the principal investigator.

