
### Statistical analysis and sample size

Negative binomial regression will be used to compare fall rates between the two groups and logistic regression will be used to compare the proportion of fallers between the two groups. If the groups differ on prognostic factors (e.g., stroke severity) or on physical activity during the follow-up period (i.e., PASIPD scores) then multiple negative binomial/logistic regression will be used. Intent-to-treat analysis will be used; all individuals with some falls-monitoring data will be included in the analysis. Survival analysis may be considered if a large number of individuals do not complete the entire 12-month follow-up. Exploratory per-protocol analysis and/or comparison of fall rates between those who return for the ‘booster’ training sessions and those who do not may also be conducted. Repeated-measures analysis of variance, with group-by-time interaction, will be used to evaluate the effect of the interventions on secondary outcome measures (e.g., functional balance measures, balance confidence). The interaction effect will reveal if there is a greater pre- to post-training improvement in the perturbation training group compared to the control group.

The target sample size has been estimated using a formula for negative binomial regression described elsewhere [78]. Assuming a rate of falls in the control group of 1.75 per person per year [27], a reduction in rate of falling of 46 % in the perturbation training group [35], mean follow-up time of 11 months per person (i.e., some participants will be lost to follow-up before 12 months), level of significance (α) of 0.05, and power (1-β) of 0.8, we estimate that 37 participants per group will be required to show significant effects. From previous studies [32, 79], we expect that ~20 % of individuals will withdraw prior to completing the intervention. While many of these individuals will be willing to complete the 12-month falls monitoring period and could be included in intent-to-treat analysis, we conservatively assume that 20 % of individuals will withdraw from the study. Therefore, we will aim to recruit at least 46 participants per group (i.e., 92 participants total).

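### The fall models are chosen after looking at group differences: the stratification factors are outside the default model, and activity measured after randomisation can trigger adjustment

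*Protocol article*

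**What the plan says.** The protocol article, Statistical analysis and sample size, sets the default for the primary outcome: "Negative binomial regression will be used to compare fall rates between the two groups". Logistic regression is named in the same way for the proportion of fallers. Adjustment is conditional. The trigger begins "If the groups differ on prognostic factors (e.g., stroke severity" and continues "or on physical activity during the follow-up period (i.e., PASIPD scores) then multiple negative binomial/logistic regression will be used". The article gives no closed list of prognostic factors and no criterion for deciding that groups differ.

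Group allocation and blinding describes the randomisation: "There will be four strata based on two stratification factors: site (two levels), and frequency of ‘failures’ during baseline reactive balance control assessment (two levels". It justifies the second factor by saying that "high frequency of failure predicts falls in the community", and it expects stratification to help ensure that the "groups do not differ significantly on this prognostic factor". The statistics section names neither factor for the fall models.

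PASIPD is listed under Secondary outcomes (follow-up) and is completed about every two months after training. The secondary hypothesis in the Background is that perturbation training increases participation in daily activities. The secondary-outcomes section adds that better balance should increase participation, and that fall rates may rise with activity.

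**The concern.** There are two problems in one sentence.

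**Baseline factors.** Under correct randomisation any baseline difference is due to chance. Whether a covariate belongs in the model depends on how strongly it predicts falls, not on whether the arms happen to differ on it. The rule also works against the design. Stratification makes the arms alike on site and failure frequency, so the factor that the article itself calls prognostic is the one least likely to meet the condition. At stake are some power and a primary model that is not fixed in advance. In the logistic analysis the choice also changes the quantity reported, because adjusted and unadjusted odds ratios are different measures even without confounding.

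**PASIPD during follow-up.** This is measured after randomisation and may itself respond to training. A group difference on it may be a treatment effect, not an imbalance to be corrected. Adjusting for it replaces the total effect of training on falls with an effect at a given activity level, and that effect is no longer protected by randomisation.

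**Working it through.** **The plan's own figure.** Inputs from the sample-size paragraph: "Assuming a rate of falls in the control group of 1.75 per person per year", a 46% reduction (rate ratio 0.54, so 0.945 per year on perturbation training), mean follow-up 11/12 year, α 0.05 (taken as two-sided) and power 0.80. With dispersion k, the unadjusted formula is n = (1.960 + 0.842)² × [(1/t)(1/r0 + 1/r1) + 2k] / (ln 0.54)².
- (12/11)(1/1.75 + 1/0.945) = 1.778; (2.802)² = 7.849; (ln 0.54)² = 0.3797.
- At k = 0, n = 7.849 × 1.778 / 0.3797 = 36.75, which rounds up to the stated 37.

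The article does not state k. Other forms of the null variance give 37 at k of about 0.06 or 0.20. That is a separate matter; here k is an assumption.

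**Closed-form cost of omitting the failure stratum.** Assume two equal strata with rate ratio R and residual k = 0.5. The dispersion without the stratum is (1 + k)(1 + CV²) − 1, with CV² = [(R − 1)/(R + 1)]².
- Stratum modelled: n = 57.4 per group.
- R = 1.5: k = 0.56, n = 59.9 (4% of the sample lost).
- R = 2: k = 0.667, n = 64.3 (11%).
- R = 3: k = 0.875, n = 72.9 (21%).

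These percentages depend on equal strata. The baseline test has 5 + 5 = 10 trials and the cut-off for the high stratum is 10%, so one failure is enough and the high stratum could be large. At R = 2 with 80% in the high stratum, CV² = 0.16/3.24 = 0.049, k = 0.574 and the loss is about 5%. With 90% it is about 2.6%.

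**Simulation at 37 per group.** Assumptions: rate ratio 0.54, residual k 0.5, site rate ratio 1.3, severity rate ratio 1.5 per SD, stratified blocks of 4, 6 or 8, 1500 runs per scenario. Each pair is the unadjusted model, then the model with both stratification factors.

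| Failure-stratum rate ratio | Power | Mean model SE | Actual spread of estimate | Null rejection |
|---|---|---|---|---|
| 1.0 | 0.566, 0.576 | 0.294, 0.289 | 0.301, 0.302 | 0.069, 0.072 |
| 1.5 | 0.536, 0.561 | 0.298, 0.290 | 0.314, 0.314 | 0.052, 0.063 |
| 2.0 | 0.533, 0.569 | 0.307, 0.292 | 0.306, 0.305 | 0.060, 0.068 |
| 3.0 | 0.493, 0.553 | 0.324, 0.297 | 0.328, 0.320 | 0.056, 0.077 |

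The gain is 1 to 6 power points. The spread of the estimate barely changes; what falls is the reported standard error. At this size the stratum-adjusted Wald test is slightly liberal, so part of the gain is not real.

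**Type I error.** With 400 participants and no treatment effect, at stratum rate ratios 2 and 3, the unadjusted model rejects in 0.051 and 0.045 of runs. A conditional rule that adds severity when it differs at 5% rejects in 0.046 and 0.041. There is no inflation.

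**How often chance alone would trigger adjustment.** If m independent baseline factors were each tested at 5%, the probability is 1 − 0.95^m: 5% for one factor, 23% for five, 40% for ten. The article specifies neither m nor a test, so this is illustrative.

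**PASIPD trigger.** Assume training raises activity by d SD, activity multiplies the fall rate by A per SD, and the total rate ratio is 0.54. Adjusting for activity then targets 0.54 / A^d. The last two columns come from 1200 simulated trials of 74 participants per scenario, with a 5% test as the trigger.

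| d | A | 0.54 / A^d | Adjustment triggered | Average estimate under the rule |
|---|---|---|---|---|
| 0.3 | 1.2 | 0.51 | 24% | 0.52 |
| 0.3 | 1.5 | 0.48 | 27% | 0.51 |
| 0.5 | 1.2 | 0.49 | 56% | 0.50 |
| 0.5 | 1.5 | 0.44 | 54% | 0.46 |

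The unadjusted estimate averages 0.535 to 0.538 throughout. In these scenarios the rule makes training look better than its total effect.

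**The case against.** The strongest reply is that a condensed article need not list covariates and that an analysis plan may do so. That disposes of any complaint that a list is absent. It does not dispose of the conditional rule, which the article states and which an analysis plan following it would inherit.

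A reader might infer that the stratification factors can never enter the model. The text does not say so. Failure frequency is called a prognostic factor, and stroke severity is given only as an example, so either stratification factor could enter if judged imbalanced. The design only makes that unlikely.

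A reader might also infer that the stratification is wasted. Its stated purposes are comparable groups within each site and roughly equal numbers, and these are met whatever model is fitted. The precision of the estimate is essentially kept; only the reported uncertainty fails to use the strata.

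Nor should the 4%, 11% and 21% losses be read as properties of this trial. The article says that failures predict falls but not how strongly, and it does not give the stratum sizes.

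On PASIPD, the article has a sensible motive: more activity could mask a benefit on falls. That is a fair exploratory question, but it does not justify letting a post-randomisation difference decide the primary model.

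**Conclusion.** The point holds in a bounded form. The article makes the choice of fall model depend on observed group differences, and it leaves the stratification factors out of the default model.

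For the baseline part, the harm is loss of efficiency and of prespecification, not bias or a false-positive problem. The size is about 1 to 6 power points at 37 per group, under assumed dispersion and stratum rate ratios of 1 to 3, and part of that reflects slightly liberal Wald tests.

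The PASIPD part is more serious because it changes what is estimated. In the assumed scenarios adjustment is triggered in 24% to 56% of trials, and the average estimate moves from 0.54 to between 0.46 and 0.52. Those figures need training to raise activity and activity to raise falls. The article considers both plausible but quantifies neither. If training does not change activity, this shift does not arise.

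**What to change.** - Delete the conditional adjustment rule.
- Prespecify one primary model for each fall outcome, negative binomial for rates and logistic for fallers, with group, site and baseline failure stratum whatever the observed balance.
- Optionally add baseline falls. Table 2 shows them recorded before training, but the article gives no recall period, so define the variable as collected.
- Report the unadjusted comparison as a sensitivity analysis.
- Keep any model adjusted for follow-up PASIPD exploratory, and label it as not estimating the total effect of training.

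The cost is analysis wording only, since all these covariates are already collected before training. The downside is a few extra parameters in a model of 74 to 92 participants, where Wald tests may be slightly liberal (null rejection up to 0.077 in the simulation at 74).

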Despite control challenges associated with executing reactive steps, individuals with impaired balance control are increasingly dependent on these stepping responses because they are the last option to prevent falling. Because stroke survivors are at a high risk of falls, it is essential to develop approaches to re-train compensatory stepping after stroke. There is compelling evidence that physical exercise prevents falls among older adults [28]; however, no exercise intervention has effectively reduced risk of falls among individuals with stroke [29, 30]. More specific exercise, that is, perturbation training involving repeated exposure to applied balance disturbances, is necessary to achieve improvements in the control of fast reactive movements [22, 31–34]. Perturbation training is an emerging and promising treatment strategy for preventing falls [35]. The novelty of perturbation training is in the focus on speed of processing and execution of limb movements, as well as rapid restabilization; this differs from ‘traditional’ balance training programs using voluntary movements that allow participants to control speed. Such training is specific to the demands of balance recovery reactions to prevent a fall following a ‘real life’ loss of balance.

The primary objective of this study is to determine if a novel perturbation-based training program focused on improving reactive stepping in individuals with chronic stroke will reduce the risk for falls in the community. Secondary objectives are to determine the effect of perturbation training on balance confidence and activity restriction, and functional balance and mobility. Our primary hypothesis is that individuals with chronic stroke who complete perturbation training will be less likely to experience a fall up to 12-months following completion of the program, compared to individuals who complete a ‘traditional’ balance training program (control group). Our secondary hypothesis is that, compared to individuals in the control group, individuals with stroke who complete the perturbation training program will show: increased balance confidence; increased participation in daily activities in the year following completion of the program; and greater gains in functional balance and mobility.

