#### Primary outcome – falls

A fall is defined as “an event that results in a person coming to rest unintentionally on the ground or other lower level” [14]. Participants will complete a 12-month falls monitoring period after the initial 6-week training period. Participants will be provided stamped addressed postcards containing a calendar to record falls, which they will complete daily. Participants will be asked to return each postcard to the research team fortnightly. Participants will receive a monthly study newsletter by mail containing health-related articles of interest, as well as a reminder to complete the postcards. If a participant does not return a postcard within two weeks, the research assistant will call them. In this telephone call, the research assistant will try to ascertain if the participant has experienced a fall in the previous two weeks. This method is considered the ‘gold standard’ for falls reporting [53]. Participants who report a fall on the calendar will be contacted by the research assistant to complete a short questionnaire in order to determine the cause and consequences of the fall.

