#### Secondary outcomes (follow-up) – activity and participation

Fall rates may increase with increasing physical activity and mobility [54–60]. It is likely that when an individual with reduced balance control attempts to mobilize, s/he is at increased risk of losing balance and falling [61, 62]. Therefore, it is important to determine if fall rates are influenced by physical activity [63]. Conversely, improved balance control and reduced fear of falling should increase participation in activities. Physical activity and participation will be evaluated with the Physical Activity Scale for Individuals with Physical Disabilities (PASIPD [64]) and the Subjective Index of Physical and Social Outcome (SIPSO [65]), respectively, at six time points (every two months) during the 12-month follow-up. Regular administration of the questionnaires will provide an estimate of physical activity and participation over the duration of the follow-up period. The PASIPD is a 13-item questionnaire in which participants are asked to indicate the frequency and duration of recreational, household, and occupational physical activities completed in the previous 7 days. The PASID has been validated within a group of individuals with various physical disabilities, including those with stroke, showing good test-retest reliability (ρ = 0.77) and criterion validity when compared to accelerometer-based activity monitoring (ρ = 0.30; [66]). The SIPSO is a 10-item questionnaire that evaluates physical and social integration and participation in ‘normal’ daily life [65]. The SIPSO has good internal consistency (Cronbach’s α = 0.92) and test-retest reliability (ICC = 0.91) among those with stroke [65].

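### If the groups differ on physical activity during follow-up, the primary fall comparison is to be adjusted for it, which replaces the total randomised effect with one conditioned on a possible treatment effect

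*Protocol article*

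**What the plan says.** Falls are the primary outcome: "Participants will complete a 12-month falls monitoring period after the initial 6-week training period". The section on statistical analysis and sample size compares fall rates by negative binomial regression and the proportion of fallers by logistic regression. It then adds a condition and its consequence: if the groups differ on prognostic factors, such as stroke severity, "or on physical activity during the follow-up period (i.e., PASIPD scores) then multiple negative binomial/logistic regression will be used". No criterion for a difference is given. Only the per-protocol analysis and the comparison by booster attendance are called exploratory.

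The section on activity and participation places PASIPD among the secondary outcomes and has it completed "at six time points (every two months) during the 12-month follow-up". The same section says "Fall rates may increase with increasing physical activity and mobility" and, a little later, "Conversely, improved balance control and reduced fear of falling should increase participation in activities". The secondary hypothesis in the Background includes "increased participation in daily activities in the year following completion of the program". Table 2 shows that PASIPD is also taken at the pre-training assessment.

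**The concern.** The rule treats two kinds of variable alike. Stroke severity at enrolment is a baseline prognostic factor, and a group difference in it can only be chance. Activity during follow-up is recorded after randomisation and after training, so a difference in it may be something that training caused.

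By the article's own reasoning, activity may lie on the path from training to falls. A model that conditions on it asks how falls compare at equal activity. The primary objective asks whether training reduces falls in the community, with whatever change in activity comes with it. The two answers can differ. Activity and falls are also recorded over the same 12 months, so a fall may lower later PASIPD scores, and the covariate may partly be a consequence of the outcome.

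Because the switch depends on the observed PASIPD difference, the trial's data would decide which of the two questions the primary analysis answers.

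**Working it through.** **Plan figure used.** The article gives no figure for this adjustment. The only plan figure needed is 37 evaluable participants per group. With rates of 1.75 and 1.75 × 0.54 = 0.945 per person-year, 11/12 year of follow-up, two-sided α of 0.05 (sidedness assumed), power 0.80 and no overdispersion:

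n = (1.960 + 0.842)² × (12/11)(1/1.75 + 1/0.945) / (ln 0.54)² = 7.849 × 1.778 / 0.3797 = 36.75, so 37.

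That calculation has no activity covariate. It was made for the plain two-group comparison.

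**Assumed inputs.** The documents give neither the effect of training on PASIPD nor the slope of falls on PASIPD. Let d be the shift in PASIPD due to training, in SD, taken as 0.2 to 0.5. Let g be the fall rate ratio per SD of PASIPD, taken as 1.1 to 1.5.

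**Case A: no common cause of activity and falls, PASIPD taken at face value.** In a log-linear model, adjusted ratio = total ratio × g^(−d).
- g = 1.1, d = 0.2: factor 0.981
- g = 1.25, d = 0.3: factor 0.935
- g = 1.5, d = 0.5: factor 0.816

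A large-sample Poisson simulation (400,000 participants, slopes 1.2 and 1.5) agrees. A true total ratio of 1.00 became 0.96 to 0.81 after adjustment, and 0.54 became 0.52 to 0.44. Without the covariate the simulation returned the true total ratio to within about 0.01.

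**Case B: the same ranges apply to true activity, and PASIPD reflects it with correlation ρ = 0.30.** The article reports 0.30 as criterion validity against accelerometer-based monitoring. Adjusting for PASIPD then removes only a share ρ² = 0.09 of the path: factor = g^(−0.09d).
- g = 1.1, d = 0.2: 0.998
- g = 1.5, d = 0.5: 0.982

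**Case C: an unmeasured common cause, such as frailty.** Assume correlation 0.5 with activity and a log fall-rate slope of −0.5. Then factor = exp{−d(ln g − 0.25)}, since 0.5 × 0.5 = 0.25.
- g = 1.2, d = 0.5: exp(0.034) = 1.034
- g = 1.5, d = 0.5: exp(−0.078) = 0.925

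The simulation gave 0.92 to 1.04 for a true ratio of 1.00, and 0.50 to 0.56 for a true ratio of 0.54. In the same setting the direct effect was 0.82 to 0.96 and 0.44 to 0.52. The adjusted ratio need therefore match neither the total nor the direct effect, and the direction of bias is not fixed.

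**How often the rule would apply.** If a difference means p < 0.05, an assumption that the article does not state, the probability at 37 per group is Φ(d√18.5 − 1.96) + Φ(−d√18.5 − 1.96):
- no shift: 5%
- 0.2 SD: 14%
- 0.3 SD: 25%
- 0.5 SD: 58%

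At 46 per group the last three are 16%, 30% and 67%. Under Case B the PASIPD shifts are 0.3 × 0.2 = 0.06 SD and 0.3 × 0.5 = 0.15 SD, which give about 6% and 10% at 37 per group. In either case the switch is more likely the more training has changed activity.

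These figures concern the rate ratio. The odds ratio for fallers was not worked out.

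**The case against.** Four points can be made for the plan.

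**The adjustment is conditional.** A reader might infer that the primary comparison will always be adjusted. The text does not support that: the two-group models come first, and adjustment follows only on a difference. This point stands. It does not go on to establish that the unadjusted result stays primary. The article says that the adjusted model will be used and keeps the exploratory label for other analyses.

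**The expected effect on PASIPD is inferred.** A reader might take the article to predict a rise in PASIPD itself. The statements it makes concern participation, which is assigned to SIPSO, while PASIPD measures physical activity. This stands as a limit on wording. The inference is still reasonable, because the article groups activity with participation and names activity restriction in its secondary objectives.

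**The bias may be small.** A reader might conclude that a training with no net effect would be reported as an 18% reduction in falls. That is the extreme corner of assumed inputs. If PASIPD tracks true activity at only 0.30, a 0.5 SD shift and a 1.5-fold rate per SD of PASIPD would need a true shift of 0.5/0.3 = 1.67 SD and a rate ratio of exp(ln 1.5/0.3) = 3.9 per true SD. Nor is a spurious benefit the only possible direction, as Case C shows. This stands, with the caveat that an accelerometer is itself imperfect, so 0.30 may understate the validity of PASIPD.

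**The adjustment has a purpose.** The article treats activity as exposure to fall risk and wants to know whether it influences fall rates. Falls at equal activity is a fair secondary question. It does not answer the primary objective, and the article does not label it as secondary.

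**Conclusion.** The point holds as a defect in a stated rule. When the groups differ on follow-up PASIPD, the plan moves the primary fall comparison to a model that conditions on a post-randomisation secondary outcome. That model does not in general estimate the total randomised effect, and whether it is used depends on the data.

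The defect rests on the article's own text and not on any assumed number. Its size does rest on assumptions. The factor on the rate ratio runs from 0.98 to 0.82 if PASIPD is taken at face value, and from about 0.998 to 0.98 if the same ranges apply to true activity measured at 0.30. It may fall on either side of 1 if activity and falls share a cause. The documents do not allow a choice between these cases, so neither a large bias nor a fixed direction should be claimed. The point should be settled before the analysis, because the rule governs the trial's main result.

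**What to change.** Remove follow-up PASIPD from the primary negative binomial and logistic models, and drop the condition that covariates enter only if the groups differ. State that the primary intent-to-treat model contains treatment and prespecified pre-randomisation covariates only, for example site, the baseline failure stratum and baseline PASIPD.

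Keep follow-up PASIPD as an outcome compared between groups. If falls relative to activity are of interest, report an activity-adjusted model as a labelled exploratory analysis beside the primary result and not in its place.

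The cost is a sentence or two in the analysis section. Baseline PASIPD is already collected, no data collection changes, and the planned 37 per group (46 recruited) is unaffected because it was calculated without the activity covariate.

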### Trial interventions

Interventions will be administered on a 1:1 basis (i.e., one physiotherapist per participant) by a trained and licensed physiotherapist. Interventions will follow a general guide but will be tailored to the individual participants’ ability, and individualized instructions and task modifications will be used to target participant-specific impairments in balance control. Participants will complete two 1 h training sessions per week for 6 weeks. Additionally, participants will be asked to return for two 1 h ‘booster’ training sessions 3 and 9 months following the initial training period. These booster sessions may help participants to retain some of the benefits of training [40, 41]. The proposed amount of training is similar to previous studies of perturbation training [32, 34, 42, 43]. To help to alleviate barriers to attending the program we will compensate participants for their travel expenses.

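### The optional comparison of booster attenders with non-attenders is open to bias in either direction, because attendance is self-selected inside the falls window; a minor point with a simple repair

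*Protocol article*

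**What the plan says.** Three parts of the protocol article bear on this.

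- **Trial interventions.** After the six weeks of training, "participants will be asked to return for two 1 h" booster "training sessions 3 and 9 months following the initial training period". This applies to both arms. Attendance is invited, not randomised.
- **Primary outcome – falls.** "Participants will complete a 12-month falls monitoring period after the initial 6-week training period". The falls clock and the booster clock therefore start together, and both boosters lie inside the outcome window. Falls are marked daily on calendar postcards, so each is dated.
- **Statistical analysis and sample size.** Under intent to treat, "all individuals with some falls-monitoring data will be included in the analysis". The section then permits, as something that may be done, an "Exploratory per-protocol analysis and/or comparison of fall rates between those who return for the" boosters and those who do not. It does not restrict the comparison to falls after a booster, and it mentions no landmark, time-dependent exposure or adjustment. The earlier sentence on multiple regression concerns differences between the randomised groups, so it does not supply the missing adjustment.

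**The concern.** The two groups are formed by an event that happens during the period in which the outcome is counted. Falls in months 0 to 3 cannot result from any booster, and falls in months 3 to 9 cannot result from the second, yet a 12-month rate includes both. If a fall, an injury or general frailty makes a person less likely to return, those falls count against the non-attenders and help explain why they are non-attenders. A participant who leaves before month 3 or 9 cannot attend, but stays in the data with a shorter follow-up and would count as a non-attender unless excluded.

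At stake is the reading of a secondary result. Trial interventions says that boosters may help to preserve training gains. A low rate ratio among attenders could be taken as support for that, although the comparison cannot provide it.

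**Working it through.** **Inputs from the document**

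- Control fall rate: "Assuming a rate of falls in the control group of 1.75 per person per year".
- Planned effect: "a reduction in rate of falling of 46 % in the perturbation training group", so rate ratio 1 − 0.46 = 0.54.
- Follow-up in the sample-size calculation: "mean follow-up time of 11 months per person". Withdrawal: 20 %.
- Boosters at months 3 and 9; outcome window months 0 to 12.

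**The plan's own figure.** The document computes nothing for the booster comparison. Its sample size shows what is known about the over-dispersion k, which matters below. With n = (1.960 + 0.842)² × [(1/1.75 + 1/0.945)/(11/12) + 2k] / (ln 0.54)²:

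- at k = 0, n = 7.849 × 1.778 / 0.3797 = 36.75, so 37 per group, as stated;
- 37/0.8 = 46.25, against the stated 46.

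The document states no k, and 37 corresponds to k = 0. The check therefore runs from k = 0 to k = 1.

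**Main model (boosters do nothing).** One million simulated participants per scenario. Each has a gamma frailty with mean 1 and variance k, and Poisson falls in four quarters with mean 1.75/4 = 0.4375 × frailty. Attendance at months 3 and 9 follows logit(p) = 1.5 − g × (falls so far), which is p = 0.82 with no falls. No dropout. Attenders of both boosters are compared with everyone else on the crude 12-month rate. The slope g, the intercept, k and this definition of attender are assumptions.

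| k | g = 0 | g = 0.2 | g = 0.4 | g = −0.2 (fallers keener) |
|---|---|---|---|---|
| 0 | 1.00 | 0.89 | 0.78 | 1.10 |
| 0.5 | 1.00 | 0.80 | 0.64 | 1.19 |
| 1 | 1.00 | 0.72 | 0.53 | 1.28 |

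The second decimal moves by about 0.01 between runs. The true rate ratio is 1.00 in every cell.

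**Where the difference comes from.** At k = 1, the rate ratio for months 0 to 3 alone, before any booster, is already 0.65 (g = 0.2) and 0.44 (g = 0.4).

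**Is it enough to count only later falls?** At k = 0, counting only falls after month 9 gives about 1.00. At k = 1 it still gives about 0.82 and 0.67, because attenders are on average less frail. With a month-9 landmark, later falls only, stratified by the number of earlier falls, the rate ratio at k = 1 returns to about 1.00 for both slopes.

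**Second model, with 20 % loss over 12 months.** Attendance probability is 0.85 per booster for a person without falls, and only falls since the previous booster point affect attendance. Results for k = 0, 0.5 and 1:

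- attendance and dropout unrelated to falls or frailty: 1.00, 1.00, 1.00;
- each fall lowers the odds of attending by 20 %: 0.92, 0.85, 0.80;
- by 40 %: 0.81, 0.68, 0.58;
- attendance random, but frailer people leave sooner: 1.00, 0.90, 0.83;
- each fall raises the odds by 25 %: 1.07, 1.14, 1.18.

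If frailty itself, not recorded falls, lowers attendance (odds ratio 0.6 per unit of frailty), an unadjusted month-3 landmark gives 0.76 at k = 0.5 and 0.59 at k = 1. Recorded falls capture frailty only in part, so even an adjusted landmark may keep some confounding.

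**The case against.** The strongest reply is that this is the weakest commitment in the section: exploratory, one of two alternatives, and optional. The sentence fixes no counting window, model, covariates or definition of attender. It speaks of rates, not totals, and a full analysis plan could specify a landmark within its wording. No hypothesis concerns boosters, and no passage plans a decision on programme delivery from this result. Most of this stands, and it sets the severity. It does not remove the point: the document names a comparison of self-selected groups, and read as written it is crude. An exploratory label warns of chance findings, not of systematic bias.

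A reader might go further and infer any of the following, none of which the documents support.

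- **That the comparison will favour boosters.** The direction is unknown. If people who fall are keener to return, boosters appear harmful.
- **That the timing alone creates the bias.** It does not. When attendance and dropout are unrelated to falls and frailty, the rate ratio is 1.00.
- **That the bias is as large as the planned treatment effect (0.54).** A value of that size arises only by pairing the steepest slope tried with k = 1. The documents support neither value.
- **That the trial's main result is at risk.** The primary comparison is by randomised group under intent to treat and does not use booster attendance.

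**Conclusion.** The point holds as a minor one. A crude fall-rate comparison by booster attendance, with boosters at months 3 and 9 of the 12-month window, cannot separate an effect of the booster from the reasons people return. With boosters that do nothing, the main model gives about 0.89 to 0.78 (k = 0) and 0.72 to 0.53 (k = 1) when each earlier fall lowers the log-odds of attending by 0.2 to 0.4, and about 1.10 to 1.28 when each raises them by 0.2. These figures illustrate what could happen and do not predict this trial's result: slopes, baseline attendance and k are all assumed. The bias requires that falls, frailty or loss to follow-up influence attendance. That is plausible in this population but not established by the document.

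**What to change.** Replace the crude comparison with a landmark analysis at each booster, or drop it. At month 3 and again at month 9:

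- include only participants still in follow-up;
- classify them by attendance at that booster;
- count only falls after it;
- adjust for falls before it, randomised group and baseline failure stratum;
- report the result as descriptive and non-causal.

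This takes a sentence or two and no new data, since the calendars date each fall and the failure stratum is recorded at randomisation. The price is precision. Taking 37 people per group followed throughout at the planned rates, 12 months yields 37 × 1.75 + 37 × 0.945 ≈ 100 falls; months 3 to 12 yield three quarters of that, about 75; months 9 to 12 yield a quarter, about 25. The month-9 analysis would therefore be very imprecise, which is acceptable for an exploratory summary but should be stated. Dropping the comparison costs nothing that the trial's hypotheses need.
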